### 2.3. Randomization

Randomization takes place as soon as the eligibility requirements are met. Participants are randomized into one of the four treatment arms: (1) true acupuncture and CC, (2) control acupuncture and CC, (3) true acupuncture and placebo CC, and (4) control acupuncture and placebo CC by an interactive online computer program in a central office. Using a 1 : 1 : 1 : 1 treatment ratio, there will be 250 women assigned to each treatment group and we expect the dropout rate would be 20%. The randomization is stratified within each of the participating sites by a random block algorithm. The data coordinating center (DCC) statisticians generated and validated the randomization scheme for the study before it was implemented in a web-based database system, and the study coordinator at each participating site logs on the web-based system to retrieve the randomization number after a patient is ready for it. The CC and placebo CC assignments are double-blinded, unknown to patients and study investigators except the DCC data manager. The true and control acupuncture treatments are known only to the TCM specialist (besides the DCC data manager) of the participating site that performs the randomized procedure. 

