### 2.10. Establishment of a Pregnancy Registry

The outcomes of all pregnancies will be followed after delivery or termination of gestation. We will review pregnancy and birth records of the mother and of the fetus to establish neonatal morbidity and mortality and the presence of fetal anomalies. We will extract from these records concomitant medical and obstetrical conditions, exposure information on all other medical products used, including prescription products, over-the-counter products, dietary supplements, vaccines, and insertable or implantable medical devices. We will file individual case reports for all congenital anomalies, which will be reported as serious adverse events. The ectopic pregnancies will be identified by serial hCG monitoring and pelvic ultrasound examination. The doctors performing pelvic ultrasound are blinded to the treatment groups.

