### 2.11. Sample Size Calculations

The overall live birth rate for women to receive CC is estimated to be 20% during the 4-month period according to Chinese Obstetrics and Gynecology (Second Edition). Due to lack of existing data on the effectiveness of acupuncture, we cannot rely on the literature for samples size determination. Instead we hypothesize that the order of effectiveness of the treatments is as follows: True acupuncture and CC > Control acupuncture and CC,  control acupuncture and CC > True acupuncture and placebo CC,  true acupuncture and placebo CC > Control acupuncture and placebo CC. The respective live birth rates are projected with 10% difference as follows and the average rate among four arms is 15% (Table 3).

 Using a two-sided trend test and with an effective sample of 200 per group, our study is designed to have >80% power at the significance level of 0.015 (we have three primary hypotheses). The sample size has been inflated from 200 to 250/arm to allow for a dropout rate of 20%, totally 1000 cases for four arms. 

There have been multiple trials to study the effects of CC in PCOS women. The primary aim of this trial is not to reassess the efficacy of CC. The aim is to elucidate the additional efficacy of acupuncture in combination with CC, or acupuncture alone. Acupuncture is compared with CC because CC has been demonstrated to be superior to metformin [4]. The previous study design is used as a role model since it was the best executed and most cited trials in this area. [name] chairs the Steering Committee of this trial, and [name] leads the DCC for another trial using CC in PCOS women. They have considered all related studies, although the power calculation involved inevitably some assumptions. The significance level of 0.015 is approximately 0.05/3 because in this study the overall significance level is controlled to 0.05 after correcting for the multiple comparisons involving three primary hypotheses.

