### 2.12. Data Analysis

The primary outcome is the live birth rate. Secondary outcomes include (1) ovulation rate; (2) ongoing pregnancy rate at gestation 8–10 weeks; (3) multiple pregnancy rate; (4) miscarriage rate: loss of an intrauterine pregnancy before 20 completed weeks of gestation; (5) change in hormonal profile: FSH, LH, T, SHBG, and DHEAS; (6) change in metabolic profile: glucose and insulin concentrations, cholesterol, triglycerides, HDL-C, and LDL-C; (7) side effect profile; (8) change in QOL; (9) change in symptoms of anxiety and depression; and (10) credibility assessments.

The analysis will use an intent-to-treat (ITT) approach to examining differences in the live birth rates among the four treatment arms. Primary efficacy analysis will be done by comparing the treatment groups with respect to the primary outcome of live birth using the Pearson Chi-square test. For the secondary, supportive analysis, we will fit a logistic regression model to compare the treatment arms with respect to the primary outcome of live birth, adjusting for other factors such as randomization stratification of study site and prior exposure to study medications. The analysis of other secondary outcomes measured over time will entail the application of statistical methods that have been developed for correlated data since repeated observations will be made over time on each individual. For secondary outcomes such as hormone levels, a linear mixed-effects model will be fit where the main independent variables will be treatment group, time, and their interaction as well as the designed randomization stratification factors as covariates. Logistic regression models will be used in secondary analyses to evaluate the predictive value of treatment arm, clinical site, prior exposure to CC, body mass index, and other explanatory variables on binary outcomes (e.g., singleton live birth, abortion). Cox proportional hazards models and a Kaplan-Meier method will be applied to compare time to pregnancy in the treatment groups. 

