Adverse events will be categorized and percentage of patients experiencing adverse events and serious adverse events in this trial will be documented. Chi-square tests will be performed to examine differences in the proportion of total and categories of adverse events within each treatment arm. For each Data and Safety Monitoring Board (DSMB) report, a list and summary of the reported adverse events will be presented in a blinded fashion, unless otherwise formally requested. Unblinding of treatments will take place after all participants have delivered or reported final outcomes to the DCC or when there are medical emergencies.

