Sign consent	×										
History	×										×
Urine pregnancy test	×		×	×	×	×	×	×	×	×	
Physical examination	×										×
Transvaginal ultrasound	×										×
Semen analysis	×										
Hysterosalpingogram	×										
Safety eligibility lads	×										×
Fasting phlebotomy for study parameters		×									×
Depression, anxiety, and quality of life questionnaires	×										×
Credibility check questionnaire			×		×						×
Progesterone assay	×			×		×		×		×	×
HCG assay	×			×		×		×		×	×
Acupuncture treatments (twice weekly)			×	×	×	×	×	×	×	×	
Assess adverse events and concomitant meds				×		×		×		×	×

Credibility check questionnaires are completed on the third acupuncture treatment and the last acupuncture treatment.

HCG: HCG concentrations will be measured once a week during the study period. If serum HCG concentration is elevated above 10 IU/L, pelvic ultrasound will be arranged 2 weeks later for the number of the gestational sacs and the viability of the pregnancy.

**Table 3 tab3:** The respective live birth rates in each intervention.

Interventions	True acupuncture	Control acupuncture
CC	*A* = 25%	*B* = 15%
Placebo CC	*C* = 15%	*D* = 5%

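### Congenital anomalies are counted as SAEs and the only stated measure is per patient, so this one category is expected to follow the birth rates; add a per-birth figure beside it (low priority)

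*Protocol article*

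**What the plan says.** Section 2.10 sets up a pregnancy registry: "The outcomes of all pregnancies will be followed after delivery or termination of gestation". It also fixes the classification of one type of event: "We will file individual case reports for all congenital anomalies, which will be reported as serious adverse events".

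Section 2.12 fixes the measure and the test. The measure is per patient: "Adverse events will be categorized and percentage of patients experiencing adverse events and serious adverse events in this trial will be documented". The test is stated next: "Chi-square tests will be performed to examine differences in the proportion of total and categories of adverse events within each treatment arm". The closing words of that sentence are loose, and a comparison between arms is the likely meaning. Item "7) side effect profile" is among the secondary outcomes, and the DSMB receives a blinded list and summary of adverse events.

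Table 3 projects live birth rates of 25% (A), 15% (B), 15% (C) and 5% (D). Section 2.3 says that "there will be 250 women assigned to each treatment group". The article names no per-birth or per-pregnancy denominator for any safety event.

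**The concern.** A congenital anomaly needs a conception. Counted over all women in an arm, its frequency is the product of two things: how often women in that arm have a birth, and how often a birth is affected. The trial is designed to find a difference in the first factor. If the treatments work as projected, the most successful arm is expected to show the highest anomaly percentage even when no infant carries any added risk. Conversely, a raised risk per birth in an arm with few births is spread over many women who never conceived.

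At stake is how one category of the safety tables is read. Section 3.2 leaves DSMB recommendations to judgement, without formal stopping limits, so it helps if the tables separate the two factors.

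**Working it through.** **Inputs from the article.** Live birth rates L = 25%, 15%, 15%, 5% (Table 3); n = 250 women per arm (section 2.3).

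**Assumed inputs.** The article gives no anomaly risk per birth, q. I take 3%, with a range of 1% to 6%, equal in every arm, and one infant per live birth. Background event rates, where used, are also assumptions and are taken as independent of birth.

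**The plan's own figure.** Section 2.11 says that "the average rate among four arms is 15" per cent: (25 + 15 + 15 + 5)/4 = 15%. This reproduces. The article gives no figure for the safety comparison.

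**Step 1, ratio per woman.** Expected share of women with an anomaly = L × q. Because q cancels, A:B:C:D = 25:15:15:5 = 5:3:3:1 for any q. The ratios are A to D 25/5 = 5.0, C to D 15/5 = 3.0 and A to B 25/15 = 1.67. Per birth, each ratio is 1.0.

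**Step 2, expected cases.** n × L is 62.5, 37.5, 37.5 and 12.5 births. Multiplying by q = 3% gives 1.9, 1.1, 1.1 and 0.4 cases, or 0.75%, 0.45%, 0.45% and 0.15% of women.

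**Step 3, how often this would show in the anomaly category.** Uncorrected chi-square at two-sided 0.05, 250 per arm. The A versus D columns come from exact binomial enumeration and the others from simulation.

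| q | Four-arm test rejects | A vs D test rejects | A has more cases than D | A strictly highest of four |
|---|---|---|---|---|
| 1% | 2% | 0.3% | 43% | 25% |
| 2% | 5% | 3.0% | 63% | 34% |
| 3% | 8% | 8.4% | 74% | 39% |
| 5% | 12% | 21.8% | 86% | 48% |
| 6% | 15% | 27.6% | 89% | 52% |

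**Step 4, effect on all events together.** With background rate b, the share of women with any event is 1 − (1 − b)(1 − L × q). At q = 3%:

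| b | Arm A | Arm D | A:D | Four-arm test rejects |
|---|---|---|---|---|
| 3% | 3.73% | 3.15% | 1.19 | 5.7% |
| 10% | 10.67% | 10.13% | 1.05 | 5.2% |
| 30% | 30.52% | 30.11% | 1.01 | 5.1% |

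The total test stays close to its nominal 5%.

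**The case against.** The strongest objection is that the per-randomised-woman percentage is a sound measure. It gives the total burden by assigned treatment and keeps the randomised comparison. A per-birth rate conditions on something that happens after randomisation, and with about 12.5 births in arm D it would be very imprecise. This stands: the per-woman figure must not be replaced, and the per-birth figure can only be descriptive.

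Second, much is already in place. Events are to be categorised, so anomalies can form their own line; the registry holds the numerator and the denominator; live births by arm are the primary outcome and will be published; and the DSMB sees individual events. This lowers the priority. It does not remove the point, because the article names a denominator and names only one.

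Third, a journal article leaves table layouts to the full protocol or the SAP, which may already add a per-birth rate. That is possible. The point therefore concerns the measure the article does state, and does not claim that the trial has no other.

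A reader might infer something stronger: that the arm with most births will be shown as the most harmful, or that the overall serious adverse event comparison is compromised. The documents do not support either. The 5:3:3:1 pattern holds in expectation, but with about two cases in arm A that arm is strictly highest in only 25% to 52% of trials over the assumed range of q. A large distortion appears only if pregnancy-dependent serious events reach 10%, 20% or 30% of births and no other events occur: four-arm rejection is then about 27%, 59% and 81%. Section 2.10 makes only congenital anomalies serious adverse events. It has other neonatal and obstetric findings extracted for the registry without saying that they become adverse events, and section 2.9 places the final adverse event assessment at the end-of-treatment visit. With an assumed 10% background the same three figures fall to about 7%, 15% and 28%, and with 30% to about 6%, 8% and 11%.

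**Conclusion.** The point holds for the anomaly category. Under the article's own projections, the stated measure makes the expected anomaly percentage five times higher in arm A than in arm D at equal risk per birth, so read alone it cannot separate more births from more harm. This follows from the stated classification and denominator, and does not depend on q.

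The consequence is modest. At an assumed 3% risk per birth the whole trial expects about 4.5 cases (150 births × 3%). The four-arm test on the category rejects about 8% of the time, and the test on all events about 5% to 6% over background rates of 3% to 30%. These figures rest on the Table 3 rates, an equal and assumed risk per birth, one infant per birth, and background events independent of birth. It is a cheap improvement of low priority and no threat to the trial's conclusions.

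**What to change.** In section 2.12, and in the DSMB summaries:

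- Keep the percentage of randomised women as stated, including in the totals. Taking pregnancy-dependent events out of the total is a debatable trade-off, and this point does not require it.
- Show congenital anomalies as a separate category, together with any other pregnancy-dependent events that are in fact recorded as adverse events.
- Report that category also per live birth or per pregnancy, with numerator and denominator given for each arm.
- State that the per-birth figures are descriptive, because they condition on conceiving and rest on few births.
- Reword the chi-square sentence so that it plainly says the comparison is between arms.

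The cost is a few sentences and one extra table from registry data. No new data collection is needed, and the randomised comparison is unchanged. If the SAP already contains such a table, only the wording needs to be aligned.

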## 3. Results

### 3.1. Trial Registration and Conduct

The trial has been registered at clinicaltrials.gov (NCT01573858) as well as the Chinese clinical trial registration site (http://www.chictr.org/cn/; ChiCTR-TRC-12002081), prior to the start of randomization. The study protocol, the manual of operations and procedures (MOP), CRFs, and informed consent forms have been reviewed and approved by each site participating in the study. They are in both English and Chinese versions. The principal investigators (PIs) of the protocol and the grants supporting the study are [name] and [name] of Heilongjiang University of Chinese Medicine. [name] at Yale University leads the DCC with the help of personnel from Heilongjiang University of Chinese Medicine. All study sites are monitored on a regular basis, the quality of data is tracked, and protocol deviations and violations are reported. 

### 3.2. Study Funding, Governance, and Data Sharing

The study is funded by National Public Welfare Projects for Chinese Medicine and National Trial Base for TCM and is led by a steering committee consisting of the two PIs, the leader of the DCC, an independently-selected chair ([name] of Penn State College of Medicine), site leaders and investigators, and other selected experts. Each of these individuals has one vote. Decisions are reached by majority consensus and a formal vote. The steering committee meets three times a year face to face and communicates through phone conferences or emails regularly. Additionally there are subcommittees including a protocol committee, a recruitment committee, and publication committee. 

There is an independent DSMB, which has conferences regularly via phone to review the conduct and results of the trial. The DSMB consists of both Chinese and American members, and reports are prepared in both Chinese and English. The DSMB reviews the protocol and study progress and makes recommendations during the course of this trial. For example, it reviews immediately any serious adverse events and adjudicates them. The DSMB also could recommend termination of the trial for a variety of reasons including poor recruitment, adverse effects of study medications, or a clear trend in one of the blinded treatment arms in live births exceeding our expectations. There are no formal stopping parameters for this trial. 

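### The DSMB may recommend stopping for a live-birth trend and no stopping boundary exists, so the stated overall 0.05 level is not assured.

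*Protocol article*

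**What the plan says.** Three statements in the protocol article bear on this point.

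- **Error control (Section 2.11).** There are three primary hypotheses, each tested at 0.015. The article explains that "The significance level of 0.015 is approximately 0.05/3" and that "the overall significance level is controlled to 0.05 after correcting for the multiple comparisons involving three primary hypotheses". It describes no other correction.
- **Monitoring (Section 3.2).** An independent DSMB confers regularly and reviews results as well as conduct. The grounds on which it could recommend termination include poor recruitment, adverse effects and "a clear trend in one of the blinded treatment arms in live births exceeding our expectations". Live birth is the primary outcome (Section 2.12).
- **Boundary (Section 3.2).** The same paragraph closes with "There are no formal stopping parameters for this trial".

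**The concern.** A level of 0.015 per hypothesis protects the overall 0.05 if each hypothesis is tested once, at the end. Once someone can look at the primary outcome by arm and stop the trial on what is seen, each look is a further chance of a false positive, and the correction for three hypotheses does not pay for it. An effect estimate from a trial stopped on a favourable trend also tends to be too large.

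The wording of the trigger adds a second difficulty. It refers to one arm and to expectations. Those expectations are presumably the projections in Table 3 (25%, 15%, 15% and 5%), and Section 2.11 concedes that data on the effectiveness of acupuncture were lacking when they were set. If the trigger means one arm against its projection, a cohort that conceives more readily than planned could meet it with no difference between arms. For example, Section 2.11 quotes 20% live birth on CC, while Table 3 projects 15% for CC with control acupuncture. If that arm simply achieved 20%, it would exceed its projection by 5 points without any acupuncture effect.

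**Working it through.** **Inputs from the article.** Per-hypothesis two-sided level 0.015; three primary hypotheses, A>B, B>C and C>D (Sections 1 and 2.11); equal allocation (Section 2.3); recruitment 18 months, treatment 4 months, pregnancy follow-up 9 months (Section 3.3).

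**Assumptions, because the article gives no figure.** The number and spacing of looks; a threshold of 0.015 at each look; no true difference between any arms; each contrast tested as a two-arm comparison of live-birth proportions, in normal approximation.

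**Step 1: the plan's own figure.** 0.05/3 = 0.0167, and the plan uses 0.015. The Bonferroni bound is 3 × 0.015 = 0.045, which is below 0.05. Simulating the three contrasts with their correlation (neighbouring contrasts share an arm) gives about 0.041. For a single final analysis the claim is correct, with 0.05 − 0.045 = 0.005 unspent.

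**Step 2: unadjusted looks.** For each arm, draw independent normal increments between information fractions. At fraction t, reject contrast j if |S_j − S_(j+1)| / √(2t) > 2.432, the two-sided 0.015 point. The family-wise error is the share of runs with any rejection at any look, the final one included.

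| Analyses, final included | Per hypothesis | Family-wise |
|---|---|---|
| 1 | 1.5% | 4.1% |
| 2 | 2.6% | 7.1% |
| 3 | 3.5% | 9.3% |
| 4 | 4.2% | 11.1% |

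One added look already exceeds 5%; the unspent 0.005 does not absorb it.

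**Step 3: is an early look feasible?** Take uniform accrual over 18 months and an outcome known 4 + 9 = 13 months after entry (assumptions). When recruitment closes at month 18, outcomes are known for (18 − 13)/18 = 28% of women. When the last treatment ends at month 22, the share is (22 − 13)/18 = 50%. A single unadjusted look at 28% gives about 7.6% family-wise.

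**Step 4: an explicit boundary.** With p<0.001 at two equally spaced interim looks (critical value 3.291) and 0.015 at the end, the result is about 1.6% per hypothesis and 4.4% family-wise. The 0.05 claim then holds with the final tests unchanged.

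**The case against.** The strongest reply is that the article describes no repeated significance testing. It schedules no efficacy analysis, gives no number of looks and names no interim p-value. The DSMB only recommends, a clear trend is a matter of judgement, and a board that demanded very strong evidence would keep the error below 5%, as Step 4 shows. The sentence in Section 2.11 is also expressly about three hypotheses, and on that footing it is right. All of this stands. A reader might infer that the 0.05 control has been shown to fail, or that the trial's error rate is 7% to 11%. The documents support neither inference, because those percentages depend on looks and a threshold that the article does not give.

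Slow outcomes also limit the exposure. Under the accrual assumption, looks at 67% or 75% of outcomes would come after all treatment had ended, when only follow-up could be shortened. That makes many useful looks unlikely, but one look at 28% is enough to pass 5%.

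A reader might also take the trigger as certainly a single-arm comparison with an outside expectation. The wording equally allows one arm pulling away from the others by more than projected. It is ambiguous, and the inflation figures describe only the between-arm reading.

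Two replies do not stand. Masked arm labels do not help, because live births can still be compared across coded arms. Nor is the boundary a detail that may be left to an analysis plan or charter: the article says outright that no formal parameters exist, so a boundary elsewhere would contradict it.

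**Conclusion.** The point holds in this form: the article names a trend in the primary outcome as a ground for termination, states that no formal stopping rule exists, and claims an overall level that corrects only for three hypotheses. Control at 0.05 is not assured, and the actual level cannot be calculated from what is written. The illustrative size is 7.1%, 9.3% and 11.1% family-wise for 2, 3 and 4 analyses, against 4.1% for one. It rests on equally spaced looks, an unadjusted 0.015 at each and no true differences. The ambiguous trigger is a separate weakness of the same sentence. The change should be made: a stated guarantee lacks support, and the repair is small.

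**What to change.** Choose one of two courses, and write it into the protocol and the DSMB charter.

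1. State that the trial will not be stopped early for efficacy, and delete the live-birth trend as a ground.
2. Replace that ground with a prespecified boundary on randomised between-arm comparisons. For example: at most two planned looks at stated fractions of known outcomes; a recommendation for efficacy only if one of the three primary contrasts reaches two-sided p<0.001; final tests kept at 0.015. Other boundaries would serve if the number of looks and the final level are set to match.

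Either course also removes the ambiguity over what is compared with what. The rule should be fixed before the DSMB sees live births by arm. The safety and recruitment grounds stay as they are. The cost is a sentence or two of text and somewhat less DSMB discretion on efficacy; sample size and final tests do not change.
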